### Monthly Medication Pickups

Additional study data are collected during monthly medication pickups. These include count of unused tablets and DBS collection for storage and testing for tenofovir diphosphate if the participant becomes HIV-infected. Participants are requested to bring PrEP bottles with them to their monthly medication pickup, which also permits appropriate destruction of unused medication. Participants can receive new PrEP refills if they do not have their unused tablets with them, and the study team submits a memo-to-file. We collect both tablet-count adherence data (measured as number of unused tablets at the end of the month) and self-reported SMS adherence for the purposes of having the most complete and comprehensive measures of adherence.

### Biologic Measures

One standard blood draw is done for all participants, as it is done before knowing HIV status. Blood collected is used for rapid HIV testing as outlined below. If HIV rapid test(s) is positive, blood is then tested for CD4 count and syphilis only. If rapid tests are negative, the following tests are conducted: syphilis, hepatitis B, and DBS for storage. Table 3 summarizes all laboratory tests conducted for COPE participants at each study visit.

DBS samples are used to measure study drug levels for those initiating PrEP and subsequently become HIV infected. If participant initiates PrEP at the visit or displays symptoms of acute HIV infection, a pooled NAAT test is also conducted. Study staff store blood specimens collected from quarterly study visits at least through the end of the study. Additional DBS collected from participants on PrEP at each study visit and medication pickup after PrEP initiation are stored in a −20°C freezer after drying. DBS specimens for participants prescribed PrEP who seroconvert will be shipped in bulk in dry ice to the University of Cape Town laboratory quarterly for testing. DBS from these participants will be assayed to measure levels of intracellular tenofovir diphosphate.

**Table 3 table3:** Biologic measures taken per participant, by Combination Prevention Effectiveness Study visit.

Study visit	Biologic measure
Baseline visit	HIV rapid testing Pooled NAAT^a^ Syphilis Hepatitis B DBS^b^ CD4 (if HIV-infected) Creatinine
Follow-up visit with STI^c^ screening only	HIV rapid testing Pooled NAAT Syphilis DBS CD4 (if HIV-infected)
Follow-up visit with STI and creatinine screening (for participants initiating PrEP^d^ outside of baseline only)	HIV rapid testing Pooled NAAT Syphilis DBS CD4 (if HIV-infected) Creatinine
Monthly PrEP pickup (for PrEP participants only)	DBS

^a^NAAT: nucleic acid amplification test.

^b^DBS: dried blood spots.

^c^STI: sexually transmitted infection.

^d^PrEP pre-exposure prophylaxis.

### HIV Testing

HIV testing is completed at each regular study visit at 3-month intervals. For participants initiating/restarting PrEP or for those who display signs or symptoms of acute HIV infection at a study visit, HIV testing consists of a rapid antibody test supplemented by reflex pooled NAAT testing for antibody-negative specimens. Those with symptoms of acute HIV infection are restricted from starting on PrEP until their NAAT test results return negative. Those without symptoms of acute HIV infection can initiate PrEP if interested and eligible; if the NAAT result is positive these participants are contacted, instructed to stop taking PrEP, and asked to return to the clinic as soon as possible to reduce usage of PrEP during acute infection. All HIV-positive results will be confirmed by additional rapid and/or NAATs, in accordance with the recommended HIV testing algorithm for Thailand.

To reduce the risk of drug dosing post-HIV infection, participants on PrEP are advised to return for HIV testing and clinical evaluation, even if outside of scheduled visits, if they experience possible symptoms of acute HIV infection including fever, myalgia, fatigue, oral ulcer, skin rash, sore throat, or headache. All participants who become HIV infected while on PrEP are offered TDF and FTC resistance (K65R, M184V) testing and are referred to HIV care and treatment. Participants not on PrEP are advised to return for HIV testing if they display any of the acute HIV symptoms mentioned above.

All participants found to be HIV-infected either during the screening process or during the course of the study are able to access HIV treatment and care services through the national health scheme in Thailand, which guarantees universal access to ARVs for Thai citizens. The case manager or site coordinator at each site will complete a facilitated referral for all participants who test positive for HIV, which includes CD4 count, referral letter, and case management as needed according to standard, site-specific practices.

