Candidate participants are not screened in person during recruitment events or peer or community referrals. Interested individuals are provided study information cards with a phone number, email address, and link to a website with more information about the study eligibility criteria, purpose, available clinics, and clinic hours. Interested individuals may indicate whether they would prefer to call the study offices to schedule an appointment at their own convenience or to provide their phone number and be contacted by study staff. During the initial phone call with study staff, candidate participants are informed of the study purpose and eligibility criteria and determine whether or not they would like to proceed with study recruitment. Aggregate data are collected from these phone calls on the number of individuals contacted or who contacted the study, those that were scheduled, and reasons not scheduled.

Consent is obtained from recruited young MSM and TGW, and they are screened for eligibility in private at one of the study sites. Those who are eligible are enrolled in the study. The screening visit includes an assessment of demographic criteria and rapid HIV testing. Participants identified with HIV infection complete their screening visit, including facilitated referral to care but do not attend any study follow-up visits. Participants who are determined to be living with HIV at their screening visit do not count toward the target sample size. At baseline, participants are also screened for hepatitis B and may initiate the vaccine series during follow-up, if susceptible.

Participants who are identified as being HIV-uninfected by rapid HIV testing are prospectively enrolled into the study. Enrolled participants are offered a combination prevention intervention package, with the option to initiate daily PrEP. Prospectively enrolled participants have an initial follow-up period of 12 months; participants who complete their 12-month follow-up period, regardless of PrEP initiation status, are offered the option of further extending their follow-up for another 12 months if the study timeline permits.

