Participants can initiate, discontinue, and restart PrEP at any point during the study period. Changes to PrEP use can be communicated during any study visit, via weekly SMS surveys, or can be communicated to study staff outside of study visits. Reasons for discontinuing PrEP are recorded. Participants who restart PrEP after more than 2 weeks cessation must be rescreened. Study investigators consider someone stopped on PrEP if the participant’s weekly SMS adherence measures indicate that he/she had 2 consecutive weeks with 0 to 3 doses taken, or if the participant has >16 pills remaining from the month during a medication pickup. PrEP rescreening includes HIV testing and an assessment of willingness to commit to PrEP adherence. Participants who stop PrEP may continue in the study and continue with their remaining quarterly study visits. Participants who permanently stop PrEP or who do not want to immediately restart PrEP are instructed to return all Truvada as soon as possible.

Participants who seroconvert during the study period complete a close-out survey, receive facilitated referral to care with assistance by the case manager or site coordinator at each site, are discontinued from the study and do not attend subsequent study visits.

**Table 1 table1:** Description of quarterly and semiannual study visits for the Combination Prevention Effectiveness Study for cisgender men who have sex with men and transgender women, Thailand.

Study visit	Description
Quarterly study visits (every 3 months)	Confirm participant contact and locator information Administer CASI^a^ behavioral questionnaire Assess participant experience and impacts of study participation (including adverse events and social harms) Screen for signs and symptoms of acute HIV infection Provide HIV testing (including pooled NAAT^b^ testing if the participant has symptoms of acute HIV infection) Collect DBS^c^ for storage Distribute condom and lubricant
Semiannual study visits (every 6 months)	All procedures conducted at quarterly study visits Syphilis testing Rectal swab collection for rectal gonorrhea and chlamydia testing Serum creatinine measurement and estimated creatinine clearance calculation (for participants on PrEP^d^)

^a^CASI: computer-assisted self-interview.

^b^NAAT: nucleic acid amplification test.

^c^DBS: dried blood spots.

^d^PrEP: pre-exposure prophylaxis.

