### Data Analysis

Each week of study participation at risk for HIV for each participant falls into 1 of 4 mutually exclusive categories of person-time: (1) on PrEP, good adherence; (2) on PrEP, poor adherence; (3) off PrEP, recent PrEP discontinuation (in last 30 days); and (4) off PrEP, no recent PrEP exposure. Individuals are considered at risk for HIV until the first positive HIV test result or until the last HIV negative test result in the case of administrative censoring, loss-to-follow-up, or another censoring event.

The primary outcome analysis will compare HIV incidence during person-time on PrEP (categories 1 or 2) to HIV incidence during person-time not on PrEP (categories 3 or 4), with a simplified analysis following the analytic methods used by other PrEP open-label studies, and a more complex analysis using marginal structural models to account for time-varying confounding. Secondary outcome analyses will explore whether HIV incidence differs between participants on PrEP with good versus poor adherence (category 1 vs category 2) and whether HIV incidence differs between participants not on PrEP who have recently discontinued PrEP use versus who do not have recent PrEP exposure (category 3 vs category 4).

A more complex primary outcome analysis will be conducted using marginal structural models, following the methods proposed by Robins et al [39] As participants self-select into the PrEP group, the difference in incidence between those on PrEP and not on PrEP may be biased due to confounding. Propensity score methods will be used for bias reduction for the estimation of the causal effect of being on PrEP on HIV incidence, an approach that is well documented in nonrandomized pharmacoepidemiologic studies [40]. This will be an as-treated analysis that will account for discontinuation of PrEP, and as PrEP initiation and cessation may occur over the course of follow-up, and participants may cease and restart sex work, potential confounders may be time-varying, further complicating the estimation of causal effects.

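### The protocol contradicts itself on who gets pooled NAAT at entry; if the text governs, infections already present at entry are found and handled differently in PrEP starters and non-starters

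*Protocol article*

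**What the plan says.** Four places in the article describe who gets pooled NAAT.

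- HIV Testing, naming the groups whose antibody-negative specimens go on to reflex pooled NAAT: "For participants initiating/restarting PrEP or for those who display signs or symptoms of acute HIV infection at a study visit, HIV testing consists of".
- Biologic Measures, text: "If participant initiates PrEP at the visit or displays symptoms of acute HIV infection, a pooled NAAT test is also conducted".
- Study Visits, Table 1, on quarterly HIV testing: "including pooled NAAT^b^ testing if the participant has symptoms of acute HIV infection".
- Biologic Measures, Table 3, baseline row: "HIV rapid testing Pooled NAAT^a^ Syphilis Hepatitis B DBS^b^ CD4 (if HIV-infected) Creatinine". NAAT carries no condition here, although CD4 in the same cell does. The row for follow-up visits with STI screening only also lists pooled NAAT without a condition.

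On enrolment, Recruitment and Consent says: "Participants who are identified as being HIV-uninfected by rapid HIV testing are prospectively enrolled into the study".

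On the analysis, Data Analysis says: "Individuals are considered at risk for HIV until the first positive HIV test result or until the last HIV negative test result" (the latter for censored participants), and then: "The primary outcome analysis will compare HIV incidence during person-time on PrEP (categories 1 or 2) to HIV incidence during person-time not on PrEP". Off-PrEP time there means the third and fourth categories. HIV Testing lets an asymptomatic starter begin PrEP before the NAAT result is back. A positive result leads to contact and an instruction to stop. The article does not say how such a person enters the analysis.

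**The concern.** Table 3 and the text cannot both describe baseline testing. If the text is followed, detection of infection at time zero depends on the exposure being compared. A starter who is infected but still antibody-negative is identified from the initiation specimen. An asymptomatic non-starter in the same state is enrolled as uninfected and first tests positive at a later visit, normally month 3, during off-PrEP time. The at-risk rule would then count a prevalent infection as an off-PrEP incident one.

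Both primary analyses use this person-time, so the Poisson model and the marginal structural model are both affected. Treatment and censoring weights deal with confounding and selective drop-out. They do not turn a prevalent case misread as incident back into a prevalent one. The estimate also feeds the infections averted in the cost-effectiveness analysis.

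**Working it through.** **The plan's own figure.** Inputs from Sample Size Calculation: off-PrEP incidence 8.5 per 100 PY, 50% efficacy, half of time on PrEP, power 0.8, one-sided alpha 0.025, standard error inflated by 0% to 20%.

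- Events for a hazard ratio of 0.5 (Schoenfeld): (1.960 + 0.842)² / (0.25 × (ln 0.5)²) = 65.35.
- Mean rate: (8.5 + 4.25)/2 = 6.375 per 100 PY.
- With 10% inflation, the midpoint of the stated range: 65.35 × 1.21 / 0.06375 = 1240.3 PY, without attrition. This matches 1240, although the article does not say which variant was used.

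**Planned events.** Off PrEP: 620 × 0.085 = 52.7. On PrEP: 620 × 0.0425 = 26.35.

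**Entry infections missed by the rapid test.** The article gives no length for the NAAT-positive, antibody-negative window. I assume 2 to 4 weeks, with 1 to 6 weeks as a wider range. Using the article's headcount of 620 per group, the expected number per group is 620 × 0.085 × weeks/52:

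- 2 weeks: 2.03
- 3 weeks: 3.04
- 4 weeks: 4.05

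These are upper figures for each window, because non-starters with acute symptoms also get NAAT.

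**Case A: text governs, NAAT-positive starters excluded.** Apparent ratio = 26.35 / (52.7 + x).

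| Window | x | True 0.50 reads | True 1.00 reads |
|---|---|---|---|
| 2 weeks | 2.03 | 0.481 | 0.963 |
| 3 weeks | 3.04 | 0.473 | 0.945 |
| 4 weeks | 4.05 | 0.464 | 0.929 |

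Over 1 to 6 weeks, a true 0.50 reads 0.49 to 0.45. The assumed incidence cancels from the relative shift, which here is simply weeks/52.

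**Case B: text governs, NAAT-positive starters counted as on-PrEP events.** With as many starters as non-starters, at 3 weeks: (26.35 + 3.04) / (52.7 + 3.04) = 0.527. The shift is now against PrEP.

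**Case C: Table 3 governs.** Everyone has NAAT at baseline, so there is no asymmetry of detection at entry.

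**Size against sampling error.** SE of the log ratio: √(1/52.7 + 1/26.35) = 0.239. Case A at 3 weeks shifts the log ratio by ln(55.74/52.7) = 0.056, or 0.056/0.239 = 0.23 of one SE.

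**Short off-PrEP time.** By February 2019, 445 − 330 = 115 participants had not started PrEP at baseline, and off-PrEP time was 33 PY. Expected off-PrEP events: 33 × 0.085 = 2.8. Entry infections: 115 × 0.085 × 2/52 to 4/52 = 0.38 to 0.75, which is 13% to 27% of those events. Under Case A, 0.50 would read 0.44 to 0.39. That share falls as follow-up accrues.

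**The case against.** A reader might infer that pre-existing infections certainly count as off-PrEP cases, that on-PrEP time always starts with NAAT-cleared people, and that PrEP effectiveness is therefore overstated. The document does not support any of the three as fact.

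- Table 3 is presented as the summary of all laboratory tests by visit, and it gives baseline NAAT to everyone. On that reading there is no entry asymmetry. Against this, it conflicts with Table 1 on follow-up visits and with the text beside it, so it cannot simply be taken as the governing rule.
- Asymptomatic starters may begin PrEP before the NAAT result, so on-PrEP time is not always NAAT-cleared at its start.
- The direction is not documented. The eligibility criterion of a negative baseline HIV test suggests that NAAT-positive starters are excluded. The rule of risk until the first positive test could instead count them as events, which reverses the bias.
- Not all off-PrEP time is affected. People who stop PrEP had NAAT when they started it. The 620 non-starters are therefore a simplification.

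It can also be said that handling of infections at entry belongs in a full protocol or analysis plan that is not shown. That would answer a complaint about missing detail. It does not answer a contradiction printed in the article, nor the stated testing and at-risk rules, which together treat the two groups differently if the text is followed.

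**Conclusion.** The contradiction over pooled NAAT is certain. The bias is conditional: it arises if the text overrides Table 3, and its direction depends on an unstated choice about NAAT-positive starters. Excluding them favours PrEP modestly, so that 0.50 reads about 0.48 to 0.46. Counting them moves it to about 0.53 at 3 weeks. These figures rest on an assumed 2 to 4 week window, 620 entrants per group and no reduction for symptomatic non-starters, so they are upper estimates for that window.

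At planned person-time the shift is about a quarter of one standard error and would rarely change a conclusion by itself. It matters more in relative terms if off-PrEP time stays short, which the Discussion itself expects. The point should be settled because it is a rule applied unequally to the two sides of the primary comparison, and more follow-up of the same kind dilutes it without removing it.

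**What to change.** 1. Reconcile Table 3 with Table 1 and with the text of Biologic Measures and HIV Testing, so that one statement says who has pooled NAAT at entry and at follow-up.
2. State that infections shown to be present at entry are prevalent, and exclude them from events and person-time whatever the participant's PrEP choice.
3. Where baseline NAAT was not done, test the stored entry specimen of participants whose first positive is at their first follow-up test, if the specimen is suitable. Biologic Measures provides for DBS storage at rapid-negative visits but plans DBS assays only for drug levels, so suitability needs confirming.
4. In any case, add a sensitivity analysis that starts risk time at the first negative follow-up test in both groups.

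Cost: steps 1 and 2 are wording, and step 2 removes at most a few events. Step 3 is a handful of assays. Step 4 needs no assays but gives up about three months of early person-time per participant, with the genuine early infections in it. For someone followed 12 months that is 3/12, roughly a quarter, and less for those who re-enrol for a second year. That loss is why it should be a sensitivity analysis and not the primary one.

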### Sexually Transmitted Infection Testing

Participants are screened for syphilis and rectal gonorrhea and chlamydia at their baseline study visit and every 6 months thereafter. Rectal gonorrhea and chlamydia are assessed using either provider-collected or a self-administered rectal swab depending on participant preference. Self-administered swabs have been used in prior studies with good acceptability [31]. Participants with positive results are provided treatment either at the clinic per MOPH guidelines or are supported to get STI treatment at a local health care facility. Participants reporting signs or symptoms of other STIs are evaluated and either treated on site or referred to care.

### Hepatitis B Screening

Given the current use of Truvada in current treatment regimens for hepatitis B, all prospective participants are screened for hepatitis B infection at their baseline visit. If susceptible, they can initiate the hepatitis B vaccination series at their next visit or medication pickup. Participants initiating the hepatitis B vaccine series are referred to SCC @TropMed, or a local hospital.

### Assessment of Renal Function

A serum creatinine test is completed for all participants before PrEP initiation. eCrCl is calculated using the Cockcroft-Gault formula below.

eCrCl=[[(140 age in years)actual body weight in kg](serum creatinine in mg/dL72)]

Any participant with an eCrCl of <60 mL/min is not eligible for PrEP. PrEP users complete creatinine testing every 6 months while on PrEP.

### Cost Analysis Data Collection

Broad intervention categories include community outreach and recruitment, HIV testing, condom and condom-compatible lubricant promotion, STI testing, and PrEP distribution. Community engagement and technology are also provided to support and encourage PrEP use. Costs associated with PrEP and technology use capture a majority of the costs associated with PrEP use and are a primary component of the incremental cost-effectiveness analysis.

Study participation primarily consists of visits with procedures related to the intervention, related to research questions, or a combination of the two. However, all research-related costs are excluded in cost-effectiveness analysis. In addition, participant involvement may vary across procedures, as some may be conditional (eg, given positive test result) and some may be repeated to varying degrees (eg, adherence assessment). For each program procedure, we establish the types of resources used, the value of each unit of resource, the quantity of resources used each time the procedure occurs, including the *best estimate* of the mean and the distribution or range, and the frequency with which the procedure occurs.

The majority of procedure-based costs are expected to be variable costs, as they are consumed each time the procedure occurs. These are complemented by procedure-specific fixed costs, such as the costs associated with the development of an SMS system. In addition to procedure-specific costs, there are general costs. Fixed general costs may include facility-related costs (eg, rent and utilities), electronic equipment, software, maintenance, administrative staff, and administrative overhead. General variable costs may include personnel time not directed to specific participant procedures, including staff meetings, trainings, and supervision.

A microcosting approach [32-34] is used to directly enumerate the cost of every input used in the intervention, such as staff time spent on each intervention-related activity, facility space, equipment, materials [32,34-36], and all in-kind contributions.

Procedure-specific resources are identified from walk-throughs of procedures, surveys and interviews with program staff, and review of program records. A walk-through consists of a member of the costing team performing a real-time observation of study procedures during a participant visit, beginning with initial referrals of potential participants to the study. Visits (and procedures) include the following: recruitment; eligibility screening; enrollment; PrEP education, offer, and eligibility screening; PrEP initiation; PrEP monitoring; monthly PrEP medication pickup; and quarterly study visits. Walk-throughs of visits or procedures also evaluate contingencies that may depend on test results, eligibility, or participant preferences. Through this process, the costing team identifies activities conducted and materials consumed through each procedure. Walk-throughs from the perspective of program staff are also conducted to help identify ancillary activities such as procedure-related administrative tasks. Resources needed for the prospective component of the study are assessed through observation of practices and not through human subjects activities.

Fixed and variable general costs are identified through surveys completed by program managers. Interviews with program staff and management are used to confirm the use of identified resources and to identify any additional resources that may have been missed through this process. Budgetary and other administrative records are also reviewed to identify any additional resources.

The number of units consumed during procedures is established through a combination of the abovementioned walk-throughs of procedures, direct observation of procedures, periodic surveys with study staff, and routine data collection. Data on the number of units consumed per procedure are complemented by data collection on the number of times different iterations of a procedure occurs, the number of participants receiving procedures, and the PY on PrEP per participant. Collection of these data is integrated into data collection for program evaluation (ie, study records) and data collection for the provision of clinical services (ie, participant clinical records).

From the costing data, we estimate for each procedure the mean procedure-specific cost per occurrence of the procedure. The frequency of procedures informs our estimations of the mean general costs per participant, the total costs across all participants, and the incremental cost per person-year on PrEP. The granularity of the costing data also allows estimates of alternative protocols, such as PrEP with and without adherence support, and PrEP with a reduced biological testing protocol. Data collection instruments and methods were pilot-tested and refined during the formative phase and reviewed and validated by the study partners.

